# Mannitol for cerebral oedema after acute intracerebral haemorrhage (MACE-ICH): protocol for a prospective, randomised, open-label, blinded-endpoint phase IIb trial

**DOI:** 10.1136/bmjopen-2025-103776

**Published:** 2025-07-28

**Keywords:** Clinical trials, Intracerebral Hemorrhage, STROKE MEDICINE

## Abstract

**Background:**

Acute intracerebral haemorrhage (ICH) is devastating with a 1 month mortality rate of ~40%. Cerebral oedema can complicate acute ICH and is associated with poor outcome. In patients with large ICH, the accompanying swelling increases mass effect and causes brain herniation. Mannitol, an osmotic diuretic, is used to treat cerebral oedema after traumatic brain injury, but its safety and efficacy in ICH is unclear. We aim to assess the feasibility of a phase II randomised, controlled trial of mannitol in patients with ICH with, or at risk of, cerebral oedema to inform a definitive trial.

**Methods:**

The mannitol for cerebral oedema after acute intracerebral haemorrhage trial (MACE-ICH) aims to include 45 ICH participants from 10 UK sites with estimated largest diameter of haematoma volume >2 cm, presenting within 72 hours of onset with, or at risk of, cerebral oedema (limited Glasgow Coma Scale (GCS)<9, including motor and visual components only, and National Institutes of Health Stroke Scale>8) with or without mass effect. Participants will be randomised (1:1:1) to 1 g/kg 10% single-dose intravenous mannitol, 1 g/kg 10% mannitol followed by a second dose at 24 hours, or standard care alone. Outcome assessors will be masked to treatment allocation. Feasibility outcomes include proportion of patients approached being randomised, participants receiving allocated treatment, recruitment rate, treatment adherence and follow-up. Secondary outcomes include serum electrolytes and osmolality at days 1–2; change in ICH and oedema volume at day 5; number of participants who developed urinary tract infection, GCS and National Institutes of Health Stroke Scale at day 5±2; length of hospital stay, discharge destination and death up to day 28; death and death or dependency by day 180 and disability (Barthel Index), quality of life (EuroQol, 5-D) and cognition (telephone mini-mental state examination) at day 180.

**Ethics and dissemination:**

MACE-ICH received ethics approval from the East Midlands-Leicester Central research ethics committee (22/EM/0242). The trial is funded by a National Institute for Health and Care Research RfPB grant (203080). The results will be published in an academic journal and disseminated through academic conferences and patient support groups. Reporting will be in line with Consolidated Standards of Reporting Trials recommendations.

**Trial registration numbers:**

ISRCTN15383301; EUDRACT 2022-000283-22.

STRENGTHS AND LIMITATIONS OF THIS STUDYAcute intracerebral haemorrhage (ICH) is a devastating stroke for which treatment lags significantly when compared with ischaemic stroke. Mannitol for cerebral oedema after acute intracerebral haemorrhage trial (MACE-ICH) aims to test mannitol, which is an osmotic diuretic, as a potential treatment for cerebral oedema after ICH.This is a feasibility trial with candidate clinical and radiological outcomes to determine if a definite trial is feasible; MACE-ICH is the first trial which will compare two doses of mannitol versus standard care alone.Recruitment into MACE-ICH is based on routine clinical assessment and CT scanning, which is quick, widely available and an inexpensive imaging resource.Local investigators and clinical staff administering mannitol are not blinded, but follow-up assessments and adjudication of brain imaging will be performed by assessors blinded to treatment allocation.

## Introduction

 Acute spontaneous intracerebral haemorrhage (ICH) accounts for up to 15% of 150 000 strokes each year in the UK, and to date, management is largely supportive.^1 2^ Mortality in ICH is significantly higher compared with ischaemic stroke (~34% vs 12% at 1 month), and data from a UK-based registry indicate that up to 80% of survivors are left with significant disability long term.^3^ The clinical spectrum and prognosis vary according to age, intraventricular extension of haematoma and location, with more severity and mortality associated with lobar haematoma compared with deep subcortical location.^4 5^ One potential explanation is that non-hypertensive mechanisms such as cerebral amyloid angiopathy lead to lobar ICH, while hypertension is more associated with deep ICH.^4^ Aside from lowering blood pressure, reversal of coagulopathy and surgical evacuation of haematoma in a proportion of patients and management of ICH remains largely supportive.^1 6^ Consequently, research into complications such as cerebral oedema is warranted. Oedema starts within hours of ICH from clot retraction releasing serum into the surrounding brain, peaks at around 72 hours and continues for days following blood-brain barrier disruption and inflammation.^7^,^9^ Large ICH (~15%) causes significant swelling,^10^ and the only treatment supported by evidence is surgical decompression.^2^ However, surgery is not routinely available, and older patients with comorbidities, who comprise the majority of haemorrhagic strokes, are often ineligible. Furthermore, surgery is associated with risks and major complications.

Mannitol, an osmotic diuretic, is readily available in most UK hospitals and easy to administer intravenously. It is licensed to treat cerebral oedema and used in traumatic brain injury and hepatic encephalopathy.^11 12^ Mannitol is known to stroke physicians: some use it regularly, occasionally or never.^13^ It is known to lower intracranial pressure by drawing water from the brain interstitium into the intravascular space.^11 14^ Mannitol is also thought to reduce blood viscosity, facilitating blood flow and oxygen delivery to the brain.^9 15^ As a free radical scavenger, mannitol might act as a neuroprotectant.^9 16^ Little is known about its effects in ICH: to date, studies have been low quality and underpowered.^1317^,^19^ Guidelines do not recommend the routine use of mannitol,^1 20^ so well-designed, randomised controlled trials (RCTs) in ICH are urgently needed.^21^

## Methods

### Aim

The mannitol for cerebral oedema after acute intracerebral haemorrhage trial (MACE-ICH) aims to determine the feasibility and inform the design and conduct of an adequately powered, pragmatic prospective multicentre RCT.

### Trial design

MACE-ICH is a multicentre, UK-based, three-arm, prospective, randomised, open-label, blinded-endpoint feasibility trial. The overarching hypothesis is that mannitol will reduce cerebral oedema after ICH and thereby improve outcome. This trial is funded by the National Institute for Health and Care Research, Research for Patient Benefit Programme, and is registered with a UK-based registry (ISRCTN15383301). MACE-ICH started recruiting participants in February 2024, and the trial is scheduled to be closed in November 2025.

### Eligibility criteria

#### Inclusion

Adults (>18 years).Spontaneous ICH confirmed by CT scan with an estimated largest diameter of haematoma>2 cm.<72 hours of ictus (or from last seen healthy).Cerebral oedema with or without evidence of mass effect.At risk of cerebral oedema (limited Glasgow Coma Scale (GCS) score<9 (eye opening and motor component only) and National Institutes of Health Stroke Score (NIHSS)>8).Signed consent (patient, personal or professional representative or independent physician).

In the event that more than one scan is available for a particular patient, the investigator will assess eligibility taking into account the clinical information and the latest scan which best meets the inclusion criteria. The scan used for eligibility will be documented and collected. This pre-enrolment scan will be used to compare with the post-treatment scan at day 5±2.

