### Assessments

Participants will be assessed clinically at baseline (demographics, medical history, investigations, diagnosis of ICH) in line with local clinical practice and preinfusion (day 1) and end of treatment (day 1–2) for Arms 1 and 2. All participants will be assessed again on day 5 (±2), hospital discharge and on day 180 to gather information on interventions, adverse events, discharge data and discharge destination. Data collection forms can be found in online (https://stroke.nottingham.ac.uk/mace-ich/docs/).

All participants will have brain imaging (CT head) as part of routine care before enrolment. A second research CT head will be performed at day 5 (±2) after intervention to measure haemorrhage volume and oedema volume. The methods of scan analysis are detailed in the online supplemental document.

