### Outcomes

The primary outcome is based on feasibility: number of patients screened, rate of eligible patients randomised and reasons for non-randomisation, participants who received allocated treatment and adherence to intervention, proportion of participants followed up to day 180 and reasons for loss to follow-up, proportion of randomised participants with full outcome data and reasons for non-availability.

The following measures are expected to be secondary outcomes in a definitive trial and will be collected:

Day 1–2: U&Es; eGFR; serum osmolality to correlate response to mannitol.Day 5±2: neurological deterioration (increase in NIHSS>3); GCS; NIHSS; death; urinary tract infection; sepsis.Radiological: follow-up CT after treatment (day 5±2) for comparison with pre-enrolment imaging to assess changes in oedema volume, haematoma size/volume, maximum diameter, midline shift and hydrocephalus.Day 28: mortality; urinary tract infection; septicaemia.Day 180 (blinded central follow-up via telephone/postal interview): death or dependency (mRS) disability (Barthel Index); mood (Zung depression scale); cognition (Telephone Interview of Cognitive Status); quality of life (EuroQol 5-D); length of stay; discharge destination. The long-term outcomes post-COVID-19 and ICH are not yet fully defined and may include additional yet undefined neurological complications. These will also be collected.Number of patients transferred to the high dependency unit.Number of patients intubated and ventilated.Number of patients who underwent neurosurgical intervention.Recurrent stroke (ischaemic or haemorrhagic).

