## Discussion

The use of mannitol in ICH is promising and has been the traditional hyperosmolar agent of choice in management of cerebral oedema. MACE-ICH has therefore been designed as an open, pragmatic clinical trial to determine the feasibility of administering mannitol in adult patients with ICH and cerebral oedema or those at significant risk. This trial will inform a definite trial which will compare the safety and efficacy of a single dose of mannitol, two doses compared with standard care. If oedema is prevented or reduced, outcomes may improve.

In this trial, broad inclusion criteria have been developed to reflect the diverse presentation of patients with ICH. The clinical course in the early hours and days after ICH is dynamic, so patients who do not fit the inclusion criteria on admission will be eligible if they subsequently deteriorate and develop signs or radiological features which meet the inclusion criteria within 72 hours. The optimal timing for treatment is unknown, and the rationale for <72 hours is based on when patients are likely to develop brain swelling and/or are at risk of further expansion.^10^ The rationale for ICH with the largest haematoma diameter>2 cm is based on observational data from a blood pressure-lowering trial where such patients were at risk of poor outcome.^24^ Moreover, ICH patients with diameter>2 cm were more likely to receive mannitol in another study.^18^ Visual assessment of maximum haemorrhage diameter has been shown to have strong agreement with measured diameter. It is quick to perform and has been previously shown that the measures are reproducible.^25^ Moreover, visual assessment has the advantage that it can be applied in the absence of special measurement tools in emergency care settings.

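### The CT chosen for eligibility is also the baseline for every CT change outcome, and the selection rule does not guarantee that it is the last scan before randomisation

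*Protocol article*

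**What the plan says.** Under Eligibility criteria, Inclusion, the protocol article sets the rule for patients with more than one scan: "the investigator will assess eligibility taking into account the clinical information and the latest scan which best meets the inclusion criteria". It continues: "The scan used for eligibility will be documented and collected", and then: "This pre-enrolment scan will be used to compare with the post-treatment scan at day 5±2". The Outcomes section uses the follow-up CT "for comparison with pre-enrolment imaging to assess changes in oedema volume", and lists haematoma size or volume, maximum diameter, midline shift and hydrocephalus alongside oedema.

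The CT part of eligibility is a lower threshold: "Spontaneous ICH confirmed by CT scan with an estimated largest diameter of haematoma>2 cm". Oedema is judged by eye as a hypodense zone around the haematoma. The time criterion is "<72 hours of ictus (or from last seen healthy". On baseline imaging, Assessments says: "All participants will have brain imaging (CT head) as part of routine care before enrolment". The Discussion adds that "patients who do not fit the inclusion criteria on admission will be eligible if they subsequently deteriorate", on signs or radiological features, within 72 hours.

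**The concern.** Eligibility and baseline measurement ask different things of a scan. For eligibility, any scan that shows the criteria are met will do. For a change outcome, the baseline should lie as close before randomisation as the available imaging allows, because whatever happens between baseline and randomisation cannot be an effect of treatment. The article uses one scan for both purposes and selects it by a rule written for the first.

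Timing matters here on the article's own account. The Introduction says that oedema begins within hours of the bleed and reaches its peak at about 72 hours, which is also the limit of the enrolment window. Patients who qualify late, after deterioration, are those most likely to have been scanned more than once.

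At stake are the size and spread of the recorded CT changes. The trial's overarching hypothesis is that mannitol reduces oedema, and radiological measures are among its candidate outcomes.

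**Working it through.** The article gives no figure on this point, so there is none to reproduce. The check is a reading of the rule followed by two illustrations.

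**1. When do *latest* and *best meets* diverge?** Take a patient with an earlier scan A and a later scan B, both before enrolment.

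- A does not qualify and B does: both words point to B, the last scan.
- Both qualify and B shows a larger haematoma or more oedema: the size criterion has no upper limit, so B fits at least as well and is also the latest. B is used.
- Both qualify about equally: *best* has no content against a threshold. The plain reading gives B, but the investigator also weighs clinical information and nothing settles the matter.
- B fits less well than A, or no longer qualifies, for example because the haematoma is smaller: the two words conflict, and A can become the baseline. Haematoma change from A to B, here shrinkage, is then counted as change to day 5±2. Oedema could move either way over the same period.
- Only one scan exists: the rule has no role.

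The rule therefore often gives the last scan but does not guarantee it, and sites may apply it differently.

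**2. What enters the recorded change.** Write recorded change as D = G₁ + G₂ + C, where

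- G₁ is change from the chosen scan to the last CT before randomisation,
- G₂ is change from that last CT to randomisation,
- C is change from randomisation to the follow-up CT.

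Only C can carry a treatment effect. The selection rule governs G₁. G₂ is present whichever scan is selected, including in a patient who enters on clinical signs without a repeat CT.

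**3. How much of the interval can lie before treatment.** Inputs: follow-up at day 3, 5 or 7 (day 5±2, Assessments); the gap from baseline scan to treatment is assumed, below the 72-hour limit. Share = gap / (gap + 24 × follow-up day), in hours.

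| Assumed gap | Day 3 | Day 5 | Day 7 |
|---|---|---|---|
| 6 h | 8% | 5% | 3% |
| 24 h | 25% | 17% | 13% |
| 48 h | 40% | 29% | 22% |
| 70 h | 49% | 37% | 29% |

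For example, 24 / (24 + 120) = 17%. These are shares of time, not of volume change. They cover the whole gap to treatment (G₁ and G₂ together).

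**4. Effect on the comparison of arms.** Under Randomisation, the allocation is released only after baseline data collection, so G = G₁ + G₂ has the same expectation in every arm and cancels from the expected difference. If G and C are independent, the standard error of a difference between two arms of n is √[(2/n)(SD_C² + SD_G²)].

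Inputs: n = 45/3 = 15 from the article. All volumes are assumptions: C has mean 10 mL and SD 10 mL in controls, the true effect is −5 mL, and G has mean 6 mL in every participant.

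- No G: control mean 10 mL; SE = √(2/15 × 100) = 3.7 mL.
- SD_G = 5 mL: control mean 10 + 6 = 16 mL; SE = √(2/15 × 125) = 4.1 mL.
- SD_G = 10 mL: control mean 16 mL; SE = √(2/15 × 200) = 5.2 mL.

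Simulation (20,000 runs) agreed with these standard errors and gave mean arm differences of −5.02, −5.03 and −4.99 mL: no bias, only loss of precision. Because every participant is given pre-treatment growth, the illustration overstates the effect if few have an older baseline scan.

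**The case against.** The case on the other side is substantial.

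- *The rule does say latest.* A reader might infer that the protocol makes an older scan the baseline. It does not. On its plain reading the most recent qualifying scan is used, and where the lesion has grown both words select the later scan. This stands. What is left is a rule that leaves the baseline open when the words part.
- *Late entry proves little by itself.* A patient who later qualifies on radiological features has a non-qualifying admission scan, so that scan is not chosen. One who qualifies on signs without a new CT has the admission scan as the last CT anyway. This also stands: late entry shows that the lesion is evolving while the rule operates, not that the wrong scan is chosen.
- *The arms are not biased.* A reader might infer that the rule could systematically create or hide a treatment effect. Scan choice precedes the release of allocation, and imaging is adjudicated blind, so only chance imbalance and added noise remain.
- *Nothing downstream is sized from these data.* A reader might infer that an inflated SD would inflate the definitive trial by some percentage. The document does not say that an SD from this trial will be used. Sample size and justification carries forward rates, recruitment patterns and set-up times, and Outcomes expects these measures to be secondary in a definitive trial. It also gives no basis for the proportion of participants with an older baseline scan.
- *The scan-analysis supplement is not shown* and may define the baseline. It may, but the sentence in the Inclusion section would still need to agree with it.

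**Conclusion.** The point holds in a limited form. One scan serves for eligibility and as the baseline for all CT change outcomes, and the rule for choosing it gives no priority between recency and fit. The baseline therefore need not be the last CT before randomisation, and change before treatment, whether growth or shrinkage, can be counted as change to day 5±2. This distorts within-arm change and adds noise. It does not, in expectation, bias the comparison of arms, a conclusion that rests on the scan being fixed before the allocation is known, as the article describes.

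The consequence is modest: the outcomes are secondary, the analysis is exploratory and the primary outcome is feasibility. The size cannot be derived from the document, since it depends on how many participants have several scans, how often an earlier one is chosen and how far apart the scans are, none of which is given. The increase in standard error in the illustration also assumes that change before and after randomisation is independent. The change is still worth making, because it replaces an indeterminate baseline with a definite one at very little cost.

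**What to change.** Separate the two uses of the scan. Let eligibility rest on any qualifying scan, documented as now, and define the baseline for every CT change outcome as the last CT before randomisation. Where that scan is not the eligibility scan, collect it as well; the article at present promises collection only of the scan used for eligibility.

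Record the interval from the baseline scan to randomisation. The new definition removes G₁ but not G₂, so change before treatment in patients without a repeat CT remains. Recording the interval makes it visible and lets the exploratory analysis allow for it.

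The cost is a sentence or two in the protocol or analysis plan and a small amount of extra upload of scans already taken. No additional imaging is needed. The analysis plan is to be confirmed before database lock, so the definition can be placed there, provided that the scans are requested from sites.

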#### Assessment of maximum haemorrhage diameter and cerebral oedema for eligibility

Visual estimate of maximum haematoma diameter (>2 cm) and presence of cerebral oedema will be performed by investigators at sites prior to enrolment by reviewing the plain CT scan viewed at the local hospital. Maximum haematoma diameter is assessed as the longest haematoma diameter in any plane, based on a measurement made with the calliper tool in PACS, Picture Archiving and Communication System (if available), or by visual comparison to the image measurement scale embedded in the image. Cerebral oedema is identified as a hypodense zone surrounding the haematoma.^22^

#### Exclusion

GCS<5.Premorbid modified Rankin Scale (mRS)>3.Isolated subarachnoid haemorrhage.Haemorrhage known to be from trauma, venous thrombosis, arteriovenous malformation, brain tumour, transformation of cerebral infarct, cerebral aneurysm or thrombolytic drug.Known hypersensitivity to mannitol.Severe renal failure (eGFR (estimated Glomerular Filtration Rate)<30 mL/min or dialysis).Cardiac failure.Hypotension at baseline (SBP (Systolic Blood Pressure)<90 mm Hg).Anuria.Patient unwilling to participate.Geographical or other factors which prohibit follow-up.Pre-existing comorbidity with preictal life expectancy<6 months.Severe dementia.Planned for palliative care.Severe hypernatremia (sodium>160 mmol/L) and serum osmolality>320 mosmol/kg.Severe hyponatraemia (sodium<125 mmol/L).Women of childbearing potential with a positive pregnancy test at the time of admission or lactating.Patients in whom peripheral intravenous cannula cannot be placed.Planned neurosurgery.

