### Intervention

Participants will be enrolled equally into one of three groups (figure 2) as soon as possible after randomisation:

Arm 1: 1 g/kg 10% single-dose mannitol infusion at 10 mL/min, in addition to standard care.Arm 2: 1 g/kg 10% mannitol at 10 mL/min followed by a second dose 1 g/kg repeated at 24 hours, if the serum osmolality is <320 mOsm/kg and sodium<160 mmol/L after the first dose, in addition to standard care.Arm 3: standard care alone.

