#### Blood tests

All participants will have blood tests taken as part of routine clinical care at the time of presentation whether or not they go on to participate in the trial. Blood samples will be labelled and analysed locally at each hospital site in accordance with local practice. Each participant in Arms 1 and 2 will have one blood test for urea and electrolytes (U&Es) and serum osmolality after the infusion, and the results will be made available to the treating clinical team. Participants in Arm 2 will have a further blood test after the second infusion (figure 2).

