The use of consent from a relative, close friend or professional representative is based on large hyperacute stroke trials such as TICH-2 (Tranexamic acid for hyperacute primary IntraCerebral Haemorrhage-2 Trial). This method of consent is essential as the majority of patients will lack capacity. The rationale for 10% mannitol is that it is less likely to crystallise than the previously commonly used 20% infusion and can be stored on a ward without the need for warming cabinets.^26^ The 20% mannitol solution has high osmolality^26^ which could increase the risk of direct venous irritation and skin damage if extravasation occurs. As a result, a large number of UK hospitals, including sites which have expressed interest in this trial, have switched to using mannitol 10% infusion. There is no guidance on which concentration of mannitol is more effective, but an equivalent dose will be administered. The 10% solution is readily available and may have fewer complications. We have chosen 1 g/kg as it has been tested before and not exceeded in previous studies.^27^,^29^ A direct comparison of previous studies shows that for an average patient weighing 70 kg, doses of mannitol varied between 20 and 100 g, and this proposal is well within this range at 70 g/24 hours.^27^,^29^ We anticipate the infusion protocol to be simple and easy to implement. Patients will receive 0.9% saline if the systolic blood pressure reduces to <90 mm Hg. Using 0.9% saline in this setting is not known to worsen cerebral oedema. The trial flowchart has been carefully designed to reflect implementation in UK stroke units. Through this approach, we hope to maximise participant recruitment and clinician engagement. Input was sought from critical care physicians and pharmacists to ensure safety checks, including blood tests, blood pressure monitoring and monitoring of urine output, were incorporated into the trial protocol.

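### The entry exclusion joins the sodium and osmolality limits with 'and', so read literally a raised osmolality alone does not keep a patient out

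*Protocol article*

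**What the plan says.** The Exclusion section of the protocol article puts both limits in one item: "Severe hypernatremia (sodium>160 mmol/L) and serum osmolality>320 mosmol/kg". No other item in the article sets an osmolality limit at entry.

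The Intervention section uses the same two numbers for the second dose in Arm 2, which is given only "if the serum osmolality is <320 mOsm/kg and sodium<160 mmol/L after the first dose".

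Two other exclusions use 'or' where either condition is enough: "Severe renal failure (eGFR (estimated Glomerular Filtration Rate)<30 mL/min or dialysis" and "with a positive pregnancy test at the time of admission or lactating".

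On measurement, the Blood tests section states that "All participants will have blood tests taken as part of routine clinical care at the time of presentation". It names serum osmolality only later: each participant in Arms 1 and 2 "will have one blood test for urea and electrolytes (U&Es) and serum osmolality after the infusion". The Assessments section mentions a clinical assessment at "preinfusion (day 1) and end of treatment (day 1–2) for Arms 1 and 2", and the Discussion refers to "safety checks, including blood tests, blood pressure monitoring and monitoring of urine output, were incorporated into the trial protocol". Neither gives a sodium or osmolality threshold for the first dose.

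**The concern.** In the second-dose rule, 'and' joins conditions for giving the drug, so failing either one stops it. In the exclusion list, 'and' joins conditions for keeping a patient out, so both must be met before it acts. The same word with the same limits therefore gives strong protection before dose 2 and weak protection before dose 1.

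Mannitol is itself a hyperosmolar drug. Followed literally, the entry rule would let an already hyperosmolar patient receive 1 g/kg, although the same blood values after that dose would bar a second one. Sites that read the item differently would also be applying different eligibility rules, in a feasibility trial meant to inform the design of a definitive one.

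**Working it through.** The article states no figure to reproduce here. The check has two parts: the logic of the two rules, and the sodium range in which the wording matters.

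**Logic.** The second-dose rule permits mannitol if osmolality <320 and sodium <160. Its negation is: withhold if osmolality ≥320 or sodium ≥160. Against the entry rule:

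| Sodium | Osmolality | Entry, as written ('and') | Entry, with 'or' |
|---|---|---|---|
| ≤160 | ≤320 | not excluded | not excluded |
| ≤160 | >320 | not excluded | excluded |
| >160 | ≤320 | not excluded | excluded |
| >160 | >320 | excluded | excluded |

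As written, one of the four combinations is excluded; with 'or', three are. The 'or' version agrees with the second-dose rule except at exactly 160 mmol/L or exactly 320 mosmol/kg.

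**Range affected.** Assumption, not from the article: calculated osmolality = 2 × sodium + S, where S is glucose plus urea in mmol/L. The 'and' wording admits, and 'or' excludes, patients with 2 × sodium + S > 320 and sodium ≤ 160, that is, sodium above (320 − S)/2 and up to 160. For an assumed range of S, in whole mmol/L:

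| S | (320 − S)/2 | Lowest sodium | Osmolality there | Affected sodium | Number of values | Osmolality at sodium 160 |
|---|---|---|---|---|---|---|
| 10 | 155 | 156 | 322 | 156–160 | 5 | 330 |
| 14 | 153 | 154 | 322 | 154–160 | 7 | 334 |
| 20 | 150 | 151 | 322 | 151–160 | 10 | 340 |
| 30 | 145 | 146 | 322 | 146–160 | 15 | 350 |

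Two examples: sodium 155 with S = 14 gives 2 × 155 + 14 = 324; sodium 146 with S = 30 gives 2 × 146 + 30 = 322. Both exceed 320, and neither is excluded by the literal wording.

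**What the osmolality limit adds.** Sodium of 161 gives 2 × 161 = 322 before glucose or urea is added. Under the same formula, every patient with sodium above 160 also has osmolality above 320, so the literal rule excludes exactly the patients that sodium >160 alone would. The third row of the first table is then empty, and the osmolality limit does no work at entry.

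**The case against.** The strongest reply is that the item already means what it should. The list is made of noun phrases, and the bracket closes after the sodium value, so the osmolality condition can be read as a second exclusion tacked on. Severe hyponatraemia excludes on sodium alone, and it would be odd for severe hypernatraemia to need a second abnormal value. The 'or' in the renal and pregnancy items sits within a single condition or a single subject, so it does not settle how this 'and' should be read. This is persuasive about intent. It does not make the text unambiguous, and it supports the change rather than arguing against it.

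A tighter limit after an osmotic load than before one could be deliberate. That is clinically coherent, but the article does not state it.

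The article condenses a full protocol. That document, the forms and the trial flowchart are not available here and may set a limit for the first dose. This stands, and for the same reason the lack of a named baseline osmolality test is not counted as a fault. The point at issue is a criterion that the article does state.

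Exclusions for eGFR below 30, dialysis and anuria will catch some patients with high osmolality. They do not catch raised glucose, or raised urea with eGFR of 30 or more.

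Finally, few patients are likely to be affected, and the wider sodium ranges need glucose plus urea of 20–30 mmol/L. That is accepted.

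**Conclusion.** The concern holds, as a minor point. As worded, osmolality above 320 mosmol/kg does not exclude a patient unless sodium is also above 160 mmol/L, whereas either value at or above its limit blocks the second dose. A drafting slip is the likeliest explanation.

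The literal reading and the mismatch with the second-dose rule rest on the text alone. The sodium ranges, and the statement that the osmolality limit is redundant, rest on the assumed formula and assumed values of S. The article gives no baseline sodium, glucose, urea or osmolality data, so how many of the 45 would be affected cannot be calculated. The sample size and the planned descriptive analysis are untouched; what is at stake is patient safety and uniform eligibility across sites.

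**What to change.** Reword the item as: sodium >160 mmol/L or serum osmolality >320 mosmol/kg. Listing two separate exclusions would do equally well. Check that the eligibility form and the full protocol say the same. If a looser rule at entry than before the second dose is intended, state it and give the reason.

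Two optional additions: align the boundaries with the second-dose rule, so that exactly 160 and exactly 320 are handled alike; and, unless the full protocol already provides for it, obtain a measured or calculated osmolality from the presentation bloods before entry.

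The cost is a one-line change to the protocol and form, one more value to check before entry, and possibly a few fewer eligible patients. Routine bloods are already taken at presentation, so sites would only need to calculate osmolality or add it to the request.
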